A prospective, uncontrolled, clinical case-control database study of 10 years with 160 patients with ischemic heart disease (all were candidates for invasive treatment), who used finger palpated tenderness on the sternum as a biofeedback measure of PPS in combination with a comprehensive self-care based stress management program, showed that the intervention had a long lasting beneficial effect on mortality and healthcare expenses (Ballegaard et al., 2004). The three year risk of dying was significant lower than the general Danish population's and there was a considerable decrease in use of medication, number of hospitalization days, and a decreasing demand of invasive cardiologic treatment, which overall led to an approximately 70.000 DKK reduction of the yearly health expenses per patient (based on the costs ten years ago). These patients started with three weeks of acupuncture treatment while the self-care part was the most important contribution for the rest of the observation period (Ballegaard et al., 2004; 1999;1996).

With respect to psychosocial characteristics the patients were found to have similar characteristics as heart patients receiving pharmaceutical treatment at a hospital outpatient clinic, both being significantly different from a group of healthy controlled and a group of patients without heart disease (both  $p < 0.05$ ) (Ballegaard et al., 1996).

In the same study series, it was found that at baseline there was a significant correlation between the degree of depression and the degree of disease measured by NYHA- classification (correlation coefficient  $r = 0.4$ ,  $p < 0.001$ ), and in addition that the degree of depression at baseline correlated independently to the effect measured as change in the NYHA-classification ( $r = 0.6$ ,  $p < 0.001$ ). The intervention was found to have a significant effect on quality of life, need for medication and degree of disease (all  $p < 0.001$ ) measured by NYHA-classification (Ballegaard et al., 1999).

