#### *6.3.5 Other variables:*

- a. Frequency of clinical event: measured by a composite endpoint when one of the following occurs: 1) visit to a hospital for a cardiac reason; 2) hospitalization of cardiac causes and 3) cardiac death. Common visits to the GP will not be counted.
- b. Patient compliance: assessed by 1) number of patients who follow the program until the end of the trial, 2) personal view of the usefulness of the program on a 7 point ordinal scale, and 3) compliance of the Ull Care program as measured by the degree of integration into daily life on a binomial scale.
- c. The number of clinical stress signs based on a designed and validated questionnaire (Ballegaard et al., 2011)
- d. Changes in medication, to ensure that any observed improvement is not due to an increase in medication prescribed by physicians outside the study protocol.
- e. Use of invasive procedures (PCI and CABG).
- f. Number of days on leave due to heart disease

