## **7. Practical course (including flowchart)**

Using databases of cardiac rehabilitation patients from Gentofte and Herlev Hospital respectively approximately 600 patients with complete cardiac rehabilitation course > 6 months ago, to ensure a steady state in regard to the efficacy of the given cardiac rehabilitation, are identified. The patients are invited by letter to participate in the study.

It is expected that about 450 will accept. These are convened to an examination at Herlev Hospital Medical Department O.

All patients sign the consent form and go through the physiological preliminary examination.

Patients with PPS < 60 are ended immediately, and a subset of the first 50 patients with PPS < 45 are invited to a measuring of their body composition.

Since it is expected that 2/3 of patients have an elevated PPS measure ( $\geq 60$ ), 300 patients with PPS  $\geq 60$  are randomized to either an active or control group with 150 in each:

**Control group:** Continue their own efforts in extension of the already given cardiac rehabilitation and receive a textbook on general stress management (REHAB + CARE).

**Active group:** the same plus the Ull treatment program (REHAB + ULL).

All included patients will at baseline be offered an additional measurement of body composition.

Intervention period: 3 months.

Both the control and active group continue with the given medical treatment. If there is a change in heart condition including possible side effects of medication, the medication is adjusted according to the procedures in the rehabilitation programs at the hospital the patient is assigned to (Gentofte or Herlev Hospital). If possible, the medication should remain stable during the 3 months of the observation. The patient and the patient's own doctor are informed that the aim of the study is that any adjustment of cardiovascular medicine happen after contact with the project nurse (perhaps through a telephone hot-line).

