**Control/Active group:**

1. Control group: receive a book about general stress management
2. Active group: receive in addition to the above mentioned:

Instruction in self-measurement of PPS by a PPS instructor at home. The patient is instructed in PPS measurement, nerve stimulation and the use of the web platform in order to be able to enter their own measurements. They are not instructed in stress management. There is a 45 minute home visit in the beginning plus two visits after one and two months respectively for additional technical instruction if the PPS measure is  $\geq 60$ . In addition there are 5 telephone dialogues á 15 minutes solely for technical instruction after 1, 3, 5, 6 and 10 weeks respectively. The patients receive an Ull meter, a written user's manual and an instructional DVD.

The patients record their PPS measurements either on the web platform ([www.songheart.org](http://www.songheart.org)) or on paper at least once a week

If their PPS records show a  $PPS \geq 60$  for 7 consecutive morning measurements, the patient is contacted regarding the need for additional technical instruction.

After three months of participation in the project all patients (both groups) are called to a repetition of the baseline visit at Herlev Hospital. Those who at baseline opted to have made body composition will have the same offer again if, at the physiological examination, they have lost 3 kg or more.

The two examinations at Herlev are conducted by the same blinded nurse at baseline and the 3 month follow-up respectively.

If the success criteria for the study are met, the subsequent analysis are carried out after the 12 month observation:

Use of health services over the last 12 months before the start of the study compared to the 12 months after commencement of participation.

The prevalence of clinical events. Here a Kaplan-Meier plot analysis will be used.

The Minimal Important Difference (MID) between the active and control group is set at a 10 % improvement in the active group versus the control group.

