## 11.2 Analysis of the effect variables

Five percent (5 %) will be used as significance level in all statistic tests.

The statistical analysis will look at two groups of cardiac patients separately: 1) those patients for whom all therapeutic approaches have been exhausted and 2) the rest. One joint analysis will be made if it is statistically reasonable. The statistics are compiled on an "intention to treat basis"; meaning that all enrolled patients are included in the subsequent analysis.

In the statistical analysis, subgroup analysis will be made for the patients with the highest PPS values: e.g. all patients with  $PPS \geq 75$ ; or for the highest quartile of PPS values.

"Closed test procedure" will be used to analyze data after 3 and 12 months in terms of the assessment of the treatment effect:

- First priority hypothesis: The Ull Care program improves the degree of depression measured by a MDI depression score, measured after 3 months of intervention.
- Second priority hypothesis: The Ull Care program improves health economic variables, measured after 12 months of intervention.
- Third priority hypothesis: The Ull Care program improves the frequency of clinical events, measured after 12 months of intervention.

Baseline measurements will be co-variant variables in relation to the applied stratification variable: the degree of depression measured by the MDI scale. Data from before and after the intervention will be analyzed separately. Delta values for

the active and control group respectively will be compared to analyze a possible treatment effect. All secondary and tertiary effect variables will be analyzed after the intervention through variance and regression analysis. If the premises for the proposed statistical analysis cannot be met, non-parametric analysis is used. Quality-of-life data will be analyzed to meet the directions of each of the questionnaires. All effect data will be presented a unifying table and primary, secondary and tertiary effect variables will be listed.

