## 12. Success criteria

The result of the study will be concluded as positive, if the following results are reached:

Compared to the control group, the active group obtains a significant improvement in MDI depression score and with a therapeutic effect size of at least 0,4 when the effect in the active group is compared to the control group (see point 11.1 for exact calculation of the effect size).

When compared to the control group, the active group obtains a significant improvement in mean PPS measurement measured by a professional instructor and with a MID of 10 units on the PPS scale.

The patient does not experience any increased risk in connection with the intervention measured as no increase in blood pressure or serum cholesterol after treatment, Both parts are measured as mean values for the two variables in the active group when the baseline values are compared at the end of the treatment period.

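### The third success criterion judges safety by the active arm's own change in mean blood pressure and cholesterol, with no control comparison, confidence interval or margin

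*Protocol*

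**What the plan says.** Protocol section 12 lists three results that must be reached before the trial is called positive. The first (MDI) and the second (PPS) each require a significant improvement over the control group and a minimum size. The third, no increased risk to the patient, is "measured as no increase in blood pressure or serum cholesterol after treatment". The section then names the comparison: "Both parts are measured as mean values for the two variables in the active group when the baseline values are compared" with the values at the end of the treatment period. It gives no test, interval or margin for this criterion and does not say whether blood pressure is systolic, diastolic or both.

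Section 11.2 takes a different route for treatment effects in general: delta values for "the active and control group respectively will be compared to analyze a possible treatment effect". The flowchart in section 7.1 has blood pressure and blood samples taken at months 0 and 3, and section 7 calls both groups to the 3-month visit, so the control data exist.

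Section 7, under the description of the control and active groups, adds a consequence: "If the success criteria for the study are met, the subsequent analysis are carried out after the 12 month observation".

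**The concern.** A change from baseline within one arm mixes the effect of the programme with everything else that moved over three months. The control group is there to remove the second part, and this criterion does not use it.

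The protocol itself points to changes that both arms could share:

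- Section 1.4.6 acknowledges that these patients take drugs acting on blood pressure and cholesterol. Section 7 lets those drugs be adjusted in both arms by the same hospital procedures, with stability only an aim: "If possible, the medication should remain stable during the 3 months of the observation".
- Section 9.2.3 gives the stress-management book to everyone.
- Section 5.2 admits only patients with PPS of 60 or more, measured at the visit that also supplies baseline blood pressure. Section 1.4.1.1 reports that PPS is linked to blood pressure, so some regression to the mean is possible.

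Two errors are at stake. A programme with no effect on these variables may be recorded as failing on safety because a mean happened to rise. A programme that raises them relative to control may be recorded as safe because both arms fell.

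**Working it through.** **Inputs**

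- Patients in the active arm: 150 (section 7).
- Significance level: 5% (section 11.2). Sidedness is not stated, so two-sided is assumed.
- SD of the change in blood pressure or cholesterol: not given. The main results are therefore in SD units. Illustrations in mmHg assume an SD of 15, with a range of 12 to 18.
- Correlation between the two changes: not given; 0 to 0.3 assumed.

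The criterion carries no figure of its own to reproduce. The 150 per arm comes from the MDI calculation in section 11.1, which reproduces closely: 2 × (1.96 + 0.842)² × (9/5)² = 50.9, so 51 per group against 50 stated. Then 2 × 50/0.36 = 278, and 278 × 1.10 = 306 against 300 stated.

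**1. Literal reading, no true change and no common change.** The active-arm mean change is centred on zero, so P(no observed rise) = 0.50 for each variable, whatever the SD or sample size. For both variables the probability is 1/4 + arcsin(ρ)/(2π), which is 0.250 at ρ = 0 and 0.298 at ρ = 0.3. If systolic and diastolic pressure both count alongside cholesterol, it drops to 0.125 and 0.198.

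**2. A change common to both arms, no treatment effect.** The standard error of the active-arm mean change is 1/√150 = 0.0816 SD. The common shift that takes the pass rate from 50% to 95% (a fall) or 5% (a rise) is 1.645 × 0.0816 = 0.134 SD. At an SD of 15 mmHg that is 2.0 mmHg (1.6 to 2.4 over SD 12 to 18).

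**3. A true excess of 2 mmHg over control.** The standard error is 15/√150 = 1.225 mmHg.

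| Change common to both arms | Net change in active arm | Probability of passing (SD 12 to 18) |
|---|---|---|
| none | +2 | Φ(−2/1.225) = 0.051 (0.021 to 0.087) |
| fall of 2 | 0 | 0.50 at any SD |
| fall of 4 | −2 | Φ(2/1.225) = 0.949 (0.913 to 0.979) |

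The same harm relative to control passes anywhere from 5% to 95% of the time, depending on a drift that has nothing to do with the programme.

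**4. If only a significant increase counts.** With no change, each variable passes 97.5% of the time, and both pass 0.975² = 95% of the time if independent. With no common change, a true 2 mmHg rise passes with probability Φ(1.96 − 2/1.225) = 0.63 (0.47 to 0.73).

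**5. The between-arm comparison.** A common change cancels. The standard error of the difference is √(2/150) = 0.1155 SD, so the 95% CI half-width is 1.96 × 0.1155 = 0.226 SD. With 135 per arm it is 0.239 SD.

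**The case against.** The best defence is that increase meant significant increase, since section 11.2 sets 5% for all tests. A harmless programme would then fail only about 5% of the time on two independent variables. That cannot be excluded, but section 12 uses the word significant in its first two criteria and not in the third. On either reading the control arm is unused, and on this one a non-significant result stands in for evidence of no harm.

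Second, the between-arm comparison is planned anyway: "All effect data will be presented a unifying table and primary, secondary and tertiary effect variables will be listed", and blood pressure and cholesterol are among the tertiary variables (sections 6.3.1 and 6.3.2). This stands. A rise against control would be estimated and reported, so safety information is not lost. The defect lies in the rule that declares the trial positive.

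Third, the protocol limits drift. Rehabilitation must have ended more than six months earlier (section 7), recent changes in angina or heart-failure drugs exclude a patient (section 5.3), and all samples are run in one assay (section 9.3). The randomised office-worker study in section 1.6 also reported benefits of 10% in blood pressure and 13% in cholesterol; effects of that size would pass easily. These points make a problem less likely, but a safety rule must also work when the hoped-for benefit is absent, and 0.13 SD is a small drift.

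A reader might infer three stronger claims that the documents do not support:

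- *That a harmless programme usually fails.* This holds only on the literal reading with no common change. A common fall of just 1 mmHg at SD 15 gives Φ(1/1.225) = 0.79 for blood pressure.
- *That a failure certainly cancels the 12-month analyses.* Section 7 reads that way. But section 6.3.4 ties its condition to primary and secondary objectives, the closed test order in section 11.2 has no blood pressure or cholesterol step, and section 7.1 schedules the month-12 data without condition.
- *That medication changes bias the active arm in a known direction.* The remark in section 1.6 that "there was a considerable decrease in use of medication" comes from an uncontrolled study of a broader programme begun with acupuncture. Here medication changes are recorded (section 6.3.5), and the examining staff are blinded.

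**Conclusion.** The point holds. Section 12 states a comparison, and it is the wrong one for the conclusion drawn from it; this is not a detail left for an analysis plan. The 50%, the 25 to 30% and the 0.13 SD need no assumed SD. They rest on the literal reading, 150 active patients and, for the joint figure, a correlation between 0 and 0.3. The mmHg figures rest on an assumed SD. A true effect that is large against the standard error (about 1 to 1.5 mmHg) would decide the result itself; chance and common changes decide it when the effect is small.

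The MDI analysis is unaffected. What is weakened is the overall declaration of a positive trial. On the wording of section 7 alone, the 12-month analyses could be stopped too, and a real rise in blood pressure is when clinical events would matter most. Because other sections describe that gate differently, this is a possible consequence and not a certain one.

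**What to change.** Reword the third criterion in section 12 as a comparison with control. For blood pressure (stating systolic, diastolic or both) and for serum cholesterol, estimate the active-minus-control difference in change from baseline to 3 months, adjusted for baseline, with a 95% CI. Conclude no increased risk if the upper limit lies below a clinical margin that the investigators fix beforehand. Add one sentence to section 7 saying that the 12-month clinical-event analysis does not depend on this criterion.

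The cost is wording only: no new data, visits or patients. The downside is that a margin M (in SD units) must be chosen. With 150 per arm and no true difference, the pass probability per variable is Φ(M/0.1155 − 1.96):

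- M = 0.33 SD (5 mmHg if the SD is 15): 82% per variable, 68% for both if independent.
- M = 0.40 SD: 93% per variable, 87% for both if independent.

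The present rule, read literally, gives 50% and 25%. A true excess equal to the margin passes 2.5% of the time. If the SD is larger than assumed, a fixed margin becomes harder to meet: excluding 5 mmHg with 80% power at one-sided 2.5% needs 91, 142 or 204 patients per arm at SD 12, 15 or 18.

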## 13. Usefulness of the study and treatment in a broader perspective

By participating in the study, each patient can get a general profit from the opportunity of an additional comprehensive health check. If the findings of the study are positive, it means that the patients in the active group have an extra benefit in terms of reduced stress, improved mood and some concrete tools for better stress management. If renewed fund applications allow it, the control group will then be offered the active treatment. The study gives the surrounding society the possibility of testing the value of a new and economically inexpensive treatment in heart patients: A treatment that is expected to have a measurable impact on the patients' future health, use of health care services and patient survival. Other scientific studies have shown that if stress and depression is reduced in a heart patient, their survival is improved. As the intervention represents a paradigm shift in the treatment of chronic illness with an emphasis on a far greater self-insight and self-effort, a positive outcome will expectedly lead to a test of the intervention in people with other chronic illnesses. The study is also designed to uncover possible links between persistent stress and heart disease and which mechanisms that is responsible for the effect that a positive outcome will show.

## 14. Ethics

The study depends on an approval from the Scientific Ethics Committee. After approval, the study will be reported to [www.clinicaltrials.gov](http://www.clinicaltrials.gov). The study is also reported to the Danish Data Protection Agency. The study complies with the Helsinki Declaration.

The study will meet Danish medical guidelines of good clinical practice.

All subjects are informed orally and in writing about the study. The investigator will obtain informed written consent. All subjects receive the booklet "Your rights as a test subject in a biomedical research project", written "Participant information" and an offer of a personal oral information session in the initial letter with an invitation for participation.

There will be emphasis on the fact that the information session is about a query of participation, and that the subject has the right to bring an accompanying person.

The subject's right not to receive information on his/hers health condition and disposition to disease will be reviewed and respected.

If during the conduct of the trial new information on effect, risks and side effects appear, the subjects will be informed and a new informed consent may be obtained.

If the subject gives written permission, a spare blood sample glass (5 ml) will be stored from both baseline and the month follow-up in one of the Danish Data Protection Agency's approved bio banks (jr.nr 2005-41-5655, later 2008-41-2031, and from Dec 2009: 30122009.HEH.O.JF). These samples are stored in coded form (i.e. without CPR number) and indefinitely.

Use of the blood samples for any other purpose than what the subjects initially consented and what is referred to in this protocol will follow the usual guidelines, including a renewed reporting to the ethics committee.

Approximately 40 ml of blood per time (two times total) is taken. This includes the spare blood sample glass.

There will be no financial compensation to subjects.

## 15. Risks and rights of the participants

The patients are not deprived of other known effective treatment that are offered to similar patients at hospitals in Copenhagen, and participation in the study does not interfere with the patient's current treatment.

Blood samples are done through vein puncture and will be performed with standard equipment, which leads to a known and limited discomfort.

The DEXA scan uses low x-rays. The radiation dose is approximately 0,1 mSv per examination, which is the same as approximately 3 % of the natural background radiation every year.

By measuring the pressure threshold, some soreness or bruises may occur if the participant does not follow the instructions and says stop or stops in time.

The HRV position testing is non-invasive and without discomfort or risk to the person. The given active intervention is risk-free. Both control and active group receive a book on general stress management.

The subjects are informed that they have the opportunity to complain to the Patient Complain Board and seek compensation through the Patient Insurance Association.

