## 7.1 Flowchart:

| Visit (number)                             | 1      | 2          | 3         | 4                                  |
|--------------------------------------------|--------|------------|-----------|------------------------------------|
| Physical location                          | Herlev | Home visit | Herlev    | Data collection via public records |
| Months                                     | 0      | 0          | 3         | 12                                 |
| Window for visits                          |        | +/-7 days  | +/-7 days |                                    |
| Informed consent                           | X      |            |           |                                    |
| Questionnaires completed                   | X      |            | X         |                                    |
| Inclusion/exclusion                        | X      |            |           |                                    |
| Blood pressure, pulse, PPS and HRV test    | X      |            | X         |                                    |
| Blood sample                               | X      |            | X         |                                    |
| Assessment of medication                   | X      |            | X         |                                    |
| Randomization                              | X      |            |           |                                    |
| Registration of clinical events            | X      |            |           | X                                  |
| Consumption of healthcare services         | X      |            |           | X                                  |
| Implementation of joint treatment          | X      |            |           |                                    |
| Implementation of active treatment         |        | X          |           |                                    |
| Measurement of body composition (subgroup) | X      |            | X         |                                    |

CONSORT Flow Chart for the SongHeart study

[figure not shown]

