## 9. Methods

### 9.1 Stress measurement:

An Ull Meter is used, which is an instrument developed to measure the sensibility/activity in the polymodal nervous system corresponding to the most painful point on the sternum between costa 3-5. The point is identified by finger pressure. First the patient learns his/hers pain threshold as the instructor applies a gradually increasing pressure on the tibia with the instrument and the patient says stop when the threshold of pain/discomfort is reached. The procedure is then repeated on the most tender place on the sternum while the patient himself

applies the pressure and stops when the pain threshold is reached. The instrument then displays a number on a scale from 30 to 100, where an increased sensibility is accompanied by an increasing number, PPS; meaning that a high PPS measure reflects a high level of stress (high sensitivity) (Ballegaard et al., 2009).

The Ull Meter has the following special features:

- Hidden measurement value until the measurement is completed.
- A calculation of the sensitivity to a tenderness score on a logarithmic scale similar to the decibel scale used to estimate the limit values of sound pressure in connection with a hearing test.
- An alarm that is activated by a pressure before the occurrence of any injury.
- A special foot pad that prevents irritation of the skin to ensure that it is the pressure sensitivity of the bone that is measured and not the skin's sensitivity.

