### *The daily steps of the self-care program*

Four elements constitute the daily self-care system: measuring, cognitive reflection, action and control.

**Measuring:** PPS is measured twice a day as a fully private measure and is entered in a personal web journal, so that the person can track his/hers own development, while at the same time there is a regular external professional control.

**Reflection:** Cognitive reflection as a reaction to the actual PPS measure and its development.

**Action:** Nerve stimulation on selected acupuncture points corresponding to the

instruction. Possible further own efforts are as mentioned in the book on general stress management given to all participants (both the active and control group). The PPS measure is used as a personal feedback marker of stress, taking into account the effect of the participant's chosen effort.

**Control:** Measure the effect of any action/inaction at any time.

This four-step procedure should be done at least twice a day (morning and evening) to be preventive; it is recommended to perform the procedure morning and evening in order to promote the construction of a conditioned reflex. This reflex (i) facilitates the habit and (ii) improves the effect of the action, which is important for ad-hoc use, should the participant want to reduce his/hers level of stress acutely or if he/she experience chest pain. It is important the program is not perceived as a chore, which is emphasized to the patient.

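### The protocol names soreness and bruising as possible harms but records no adverse events, so its finding of no increased risk rests only on active-arm mean blood pressure and cholesterol

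*Protocol*

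**What the plan says.** **Risk statements.** Section 15 of the protocol states, of the pressure-threshold measurement, that "some soreness or bruises may occur if the participant does not follow the instructions and says stop or stops in time". Shortly afterwards it says: "The given active intervention is risk-free". The Summary makes the same claim under Ethics.

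**Exposure.** The measurement belongs to the intervention. In section 9.2.2, under the daily steps, "PPS is measured twice a day as a fully private measure", for an intervention period of three months. Section 9.1 describes the technique: the patient first learns the threshold through "gradually increasing pressure on the tibia with the instrument", and the procedure is then repeated at the most tender place on the sternum.

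**Success criterion.** Section 12 requires for a positive trial that "The patient does not experience any increased risk in connection with the intervention". This is "measured as no increase in blood pressure or serum cholesterol after treatment", and the comparison uses "mean values for the two variables in the active group when the baseline values are compared at the end of the treatment period".

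**Data collection.** The flowchart in section 7.1 has a row "Registration of clinical events", marked at visit 1 (month 0) and visit 4 (month 12, from public records) and blank at visit 3 (month 3). It has no adverse-event row. Section 7 makes the 12-month analyses, including clinical events, conditional on the success criteria being met.

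**The concern.** The protocol recognises one physical harm of its own procedure, and the active arm repeats that procedure at home for three months. The plan then makes absence of increased risk one of the conditions for a positive trial, but gives no route by which this harm, or any other adverse event, would enter the data. Followed exactly, the trial could be reported as showing no added risk when nobody had asked patients about the one harm it foresaw.

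Clinical events do not fill the gap. They are not registered when treatment ends, and their analysis waits on a positive result that already includes the risk criterion. If the efficacy criteria fail, the plan gives no comparison of clinical events at all.

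This is not a matter to leave to a statistical analysis plan. Which harms are collected, and when, is fixed by the variable list and the visit schedule, and an analysis plan cannot use data that were never recorded.

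**Working it through.** The plan states no figure on harms, so there is none to reproduce. The check is mainly a comparison of sections, with a short calculation for scale.

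**1. Is the named harm collected anywhere?**

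| Place in the protocol | Content | Soreness, bruising or other adverse events? |
|---|---|---|
| 6.1 and 6.2 | MDI; PPS; WHO-5; correlations of changes | No |
| 6.3.1 to 6.3.3 | Blood tests; blood pressure, pulse, PRP, BMI, DEXA, HRV; SF-36 | No |
| 6.3.4 | Use of health services | No |
| 6.3.5 | Cardiac hospital visit, cardiac hospitalization or cardiac death; compliance and perceived usefulness; stress signs; medication changes; invasive procedures; days on leave | No |
| 7.1, month 3 | Questionnaires; blood pressure, pulse, PPS, HRV; blood sample; medication; body composition | No row; the questionnaires named in the protocol are not described as asking about it |
| 9.2.2, telephone calls | Four permitted topics | Tolerability is not one, and no recording is described |

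Section 14 undertakes to inform participants if new risks or side effects emerge, but no listed procedure would collect them.

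**2. What does the section 12 risk criterion use?** Two mean values in one arm, each at baseline and at the end of treatment. The result would be the same whether 0 or 150 active patients had bruises, and whether or not cardiac events had occurred. The control arm does not enter. Section 1.4.6 itself notes that the patients receive medication affecting these variables.

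**3. When are clinical events seen?** They are registered at months 0 and 12 and analysed only if the success criteria are met. One of those criteria is the absence of increased risk, so events are examined only after that criterion has been passed.

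**4. Scale of exposure.** Inputs: two measurements a day (section 9.2.2), three months taken as 90 days, and 150 active patients (section 7).

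- Full adherence: 2 × 90 = 180 self-measurements per patient; 180 × 150 = 27,000 in the arm.
- At the 20 % compliance reported for office workers over three months (section 1.4.1.2 on domestic measuring): 0.20 × 180 = 36 per patient; 36 × 150 = 5,400 in the arm. That section says some measurements may not have been entered, so actual use could lie above this.

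**5. What recording would yield.** With zero cases among 150 patients, the one-sided 95 % upper bound is 1 − 0.05^(1/150) = 0.0198, about 2 % (rule of three: 3/150 = 2 %). The chance of seeing at least one case is 1 − (1 − p)^150:

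- p = 1 %: 78 %
- p = 2 %: 95 %
- p = 5 %: above 99.9 %

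These values of p are assumptions; the protocol gives no rate.

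**The case against.** The strongest reply is that the criterion is explicitly defined and its data are collected: blood pressure and blood samples are taken at month 3. That is correct. A reader might infer that the risk verdict rests on no harm data whatever; the documents do not support this. It rests on two measured surrogate markers, and the fault lies in how narrow they are.

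The named harm is also minor and conditional on the participant not following instructions. Section 9.1 describes an alarm meant to act before injury and a foot pad against skin irritation, and section 9.2.2 says the finger pressure should not be painful. These points bear on how serious the harm is. They are preventive measures, however, and record nothing.

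Records collected at month 12 could recover cardiac events from the first three months in both arms. This stands in part, but those data come after the verdict, are analysed only conditionally, and would not be expected to show soreness or bruising. Program completion and perceived usefulness (section 6.3.5) are indirect signs of tolerability at best.

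Three further inferences should not be drawn:

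- **That the protocol attributes the bruising to the sternum.** Section 15 names no site, and section 9.1 applies pressure to both tibia and sternum.
- **That 27,000 measurements will take place.** That figure requires full adherence and no dropout.
- **That soreness biases PPS in favour of treatment, or that a bruise unblinds the nurse.** The protocol gives no evidence of either. Added soreness would tend to raise PPS, which works against the intervention, and recording harms would cure neither problem.

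**Conclusion.** The point holds in a limited form. The protocol names a harm of pressure measurement and describes an intervention containing that measurement as free of risk; these statements must be reconciled. No listed variable or visit records the harm or any other adverse event, and clinical events are not registered at month 3. The section 12 finding of no increased risk therefore rests on mean blood pressure and serum cholesterol, compared within the active arm only and affected by medication, and on no adverse-event or clinical-event data.

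The size of the unrecorded harm is unknown. Exposure is about 36 to 180 self-measurements per active patient, assuming a 90-day period and compliance between 20 % and 100 %. With recording, zero cases in 150 followed patients would allow a statement that the risk is below about 2 %; the present plan allows none. This should be changed because the plan's own rule would support a conclusion about risk that its data cannot carry. It does not affect the primary MDI comparison.

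**What to change.** 1. In the flowchart, register clinical events at visit 3 in both arms.
2. At visit 3, in both arms, add a short self-completed form asking about soreness, bruising or skin injury at the measurement and stimulation sites since baseline. Have it returned sealed or to someone other than the blinded nurse, so that its answers cannot reveal the arm.
3. List both as variables in section 6, and report them by arm whether or not the success criteria are met.
4. In section 12, choose one of two wordings. Either limit the statement to no increase in mean blood pressure or cholesterol, or keep a statement about risk and base it on the between-arm comparison of harms as well, with the decision rule written down beforehand.
5. Reconcile the risk-free wording in the Summary and section 15 with the harm that section 15 names.

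The cost is a protocol amendment, one short form at a visit that already takes place, and separate handling of that form. No extra visit is needed.
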